### Data analysis

The data will be analyzed using SPSS version 17.0. An 'intention to treat' analysis will be carried out to assess the differences between the intervention groups and the control group regarding ADL functional status. The variations in outcome between the groups will be calculated using mixed linear model analysis. Regression analyses and (co)variation analyses will be carried out when relevant to correct for baseline differences between older people in the three groups. Survival analysis using a Cox regression model with Kaplan-Meier survival curves will be used on mortality and admission into nursing homes. As social economic status (SES), gender, age and education are assumed to be potential effect modifiers, subgroup analysis will be applied where relevant. We will also take the working experience of the participating GPs and practice nurses into account in separate analyses.

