**Methods/Design:**

The effectiveness of U-PRIM and U-CARE is being tested in a three-armed, cluster randomized trial in 58 general practices in the Netherlands, with approximately 5000 elderly individuals expected to participate. The primary outcome is the effect on activities of daily living as measured with the Katz ADL index. Secondary outcomes are quality of life, mortality, nursing home admission, emergency department and out-of-hours General Practice (GP), surgery visits, and caregiver burden.

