### Randomization and blinding

The participating general practices are randomly allocated to one of the two intervention groups (A or B) or the control group (C) by cluster randomization on the general practice level (see flowchart). Practices in group A are allocated to the U-PRIM intervention, those in group B to the U-PRIM plus U-CARE intervention and the practices in group C formed the control group. Within the 58 participating general practices, clusters are created because some general practices are working closely together at the same location. Before randomization, clusters are stratified according to the expected number of frail older people in the general practice. The cluster size is estimated based on the number of invitations for the yearly influenza vaccination per practice.

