### Sample size calculation

At present, a valid estimation of the variance in the KATZ ADL results within and between general practices cannot be given because these data are not available for Dutch populations. For that reason, a formal power analysis for the cluster-randomized trial is not possible. Therefore, it is also not feasible in this study to take into account a potential cluster effect. In line with Faber et al., [40] we assume that any randomization effect per practice will be absent. Furthermore, we assume that with an expected number of at least 5000 frail older people included, relevant effects can be found on the outcome between the clusters because the power of a trial increases if the number of clusters, subjects, or repeated measures within a subject increases.

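### The plan assumes a zero practice effect in a cluster-randomised trial, and nothing in its analysis section says that between-arm comparisons will allow for the randomised cluster

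*Protocol article*

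**What the plan says.** **Design.** Under Randomization and blinding, allocation is "by cluster randomization on the general practice level", and "clusters are created because some general practices are working closely together at the same location". The randomised unit is therefore a practice or a group of co-located practices. The abstract gives the scale: "58 general practices in the Netherlands, with approximately 5000 elderly individuals expected to participate". The number of clusters after merging is not given.

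**Assumption.** Under Sample size calculation, the article says that "a valid estimation of the variance in the KATZ ADL results within and between general practices cannot be given". From this it concludes that "it is also not feasible in this study to take into account a potential cluster effect", and it adds: "we assume that any randomization effect per practice will be absent".

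**Analysis.** Under Data analysis, the between-group comparison is described as follows: "The variations in outcome between the groups will be calculated using mixed linear model analysis". Regression and covariance analyses are to correct for baseline differences where relevant. For the two event outcomes: "Survival analysis using a Cox regression model with Kaplan-Meier survival curves will be used on mortality and admission into nursing homes". No random effect, shared frailty, robust variance or other allowance for cluster is named for any of these.

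**The concern.** Arm is constant within a cluster, so every between-arm contrast is a contrast between clusters. If patients of one practice resemble each other more than patients of different practices, an analysis that treats them as independent understates the standard error. Its confidence intervals are then too narrow and its p-values too small.

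The article does more than leave this open: its only statement on clustering is that the effect is taken to be absent. Two parts of its Discussion sit badly with that. The Design subsection expects practices to differ at the outset in screening lists, structured care plans and the presence of a practice nurse. The Feasibility and adherence subsection expects effectiveness to vary with the characteristics of the professionals. Both are reasons to expect variation between practices.

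At stake are the comparisons on mortality and nursing home admission, any between-arm regression, and, if its mixed model leaves cluster out, the primary Katz comparison. A false-positive result matters here because the article foresees broad implementation once effectiveness is shown.

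**Working it through.** The article states no power, significance level, effect size or ICC, so there is no planned figure to reproduce. The check asks how far a test that ignores clustering departs from its nominal level.

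**Inputs from the article:** 58 practices and about 5000 patients, so m = 5000/58 = 86.2 per practice.

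**Assumed inputs:** a two-sided 5% level, equal cluster sizes, the ICC values, and 40 clusters as an example of what merging might leave.

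**Formulas:**
- Design effect: DE = 1 + (m − 1) × ICC
- True standard error / reported standard error = √DE
- True two-sided error = 2 × [1 − Φ(1.96/√DE)]

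**One case in full.** At ICC 0.01: DE = 1 + 85.2 × 0.01 = 1.85; √1.85 = 1.36; 1.96/1.36 = 1.44; true error = 15.0%. The nominal 95% interval then covers 85.0% of the time.

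| Assumed ICC | DE (m = 86.2) | √DE | True error, 58 clusters | True error, 40 clusters (m = 125) |
|---|---|---|---|---|
| 0 | 1.00 | 1.00 | 5.0% | 5.0% |
| 0.001 | 1.09 | 1.04 | 6.0% | 6.5% |
| 0.005 | 1.43 | 1.19 | 10.1% | 12.4% |
| 0.01 | 1.85 | 1.36 | 15.0% | 19.0% |
| 0.02 | 2.70 | 1.64 | 23.3% | 29.3% |

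For 40 clusters at ICC 0.01: DE = 1 + 124 × 0.01 = 2.24; √2.24 = 1.50; true error = 19.0%.

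**Check on the survival analysis itself.** The formula is generic, so the Cox score (log-rank) test was also simulated with no treatment effect: 19 against 19 practices of 86 patients, one year of follow-up, a gamma-distributed practice effect on the hazard, and 2000 runs per setting. Event rates and frailty variances are assumptions. The Monte Carlo standard error at 5% is √(0.05 × 0.95/2000) = 0.5 percentage points.

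| One-year event rate | Frailty variance (approximate ICC) | Rejection ignoring cluster | Rejection with cluster-robust variance |
|---|---|---|---|
| 5% | 0 (0) | 5.0% | 3.9% |
| 5% | 0.1 (0.005) | 11.0% | 3.9% |
| 5% | 0.2 (0.011) | 15.8% | 4.2% |
| 10% | 0 (0) | 5.2% | 4.2% |
| 10% | 0.1 (0.011) | 14.6% | 3.8% |
| 10% | 0.2 (0.022) | 22.9% | 4.3% |

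The simulated errors are close to the formula at similar ICCs. The cluster-robust test stays at or slightly below its nominal level.

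**The case against.** There are four serious objections.

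1. **Silence is not a defect in an article.** Random effects, frailty terms and variance estimators are commonly left to the full protocol or analysis plan, and the Data analysis section excludes none of them. On that section alone there would be no point to make. The point stands because the article positively asserts a zero practice effect and nothing later limits that assertion.

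2. **The assertion concerns sample size.** It stands under Sample size calculation and follows from the lack of variance data. A reader might infer that the article announces an analysis that ignores clusters. It does not say so, and the carry-over to the analysis is an inference. Equally, an ICC unknown in advance prevents a power calculation but not the estimation of a cluster effect from the trial's own data. The stated reason therefore gives no ground for leaving cluster out of the analysis.

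3. **Katz is analysed with a mixed linear model, which can carry a cluster effect.** A reader might infer that the primary analysis is invalid. The article does not support that. With measurements at baseline, six months and one year, the model could contain a patient effect only, a cluster effect only, or both. The claim for Katz is conditional.

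4. **Kaplan-Meier curves are descriptive.** A reader might infer that they too are wrong. Their point estimates are not at fault. Only confidence bands or a log-rank p-value would be affected, and the article mentions neither. Whether the baseline-adjusting regressions are separate between-arm tests is also unclear; the point applies to them only where they are.

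The size of the error is also open, since the article gives neither an ICC nor a count of merged clusters. At an ICC of 0.001 the excess is one percentage point.

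**Conclusion.** The point holds in conditional form. The assumption of no practice effect is unsupported, because the article itself says that the between-practice variance is unknown and elsewhere expects practices to differ. Nothing in the analysis section sets the assumption aside for the Cox comparisons, the regressions or the mixed model.

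If those analyses follow the assumption and the ICC exceeds 0, between-arm standard errors are too small. At about 86 patients per practice they are too small by a factor of 1.04 to 1.64 over assumed ICCs of 0.001 to 0.02, which turns a nominal 5% test into one of about 6% to 23%. With an assumed 40 merged clusters the error at ICC 0.01 rises from 15% to 19%. These figures are a range under assumed values with equal cluster sizes, not an estimate for this trial. An unadjusted test keeps its level only at an ICC of 0.

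The concern is most direct for mortality and nursing home admission, both secondary outcomes. For the primary outcome it depends on the mixed model leaving cluster out.

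**What to change.** Withdraw the zero-effect assumption for the analysis, and state that every between-arm comparison accounts for the randomised cluster, meaning the merged group where practices were combined:

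- **Katz:** a mixed model with a random intercept for the randomised cluster, a within-patient covariance structure for the repeated measurements, and small-sample degrees of freedom.
- **Mortality and nursing home admission:** Cox regression with a shared frailty, or with cluster-robust standard errors, on the randomised cluster.
- **Regression and covariance analyses that compare arms:** the same rule.
- **Reporting:** the number of randomised clusters per arm and the estimated ICC.

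If the full analysis plan already does this, one sentence in the Data analysis section is enough to remove the conflict with the sample-size text.

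The cost is wording, wider confidence intervals, and possibly a different package for the clustered survival model if the named software cannot fit it. No new data and no change to the design are needed.

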## Discussion

In this paper, we present the research design and methodology of the U-PROFIT trial. This trial assesses the effectiveness of two interventions: a proactive screening and monitoring system and a nurse-led intervention program. U-PROFIT is unique because of the robust and pragmatic study design directly embedded in primary care practice, which maximizes the generalizability of the results. The integration of the U-PRIM proactive screening tool with the U-CARE nurse-led multidisciplinary intervention program, once proven effective, will provide an innovative, practical panel management approach for frail older people that can be broadly implemented in daily clinical practice. We met several challenges during the design and implementation of the U-PROFIT trial.

### Design

As mentioned, the two interventions are tested and embedded in routine clinical practice. Therefore, it s hard to create controlled experimental circumstances. We randomized on a practice level, and some practices may have already use screening lists or structured plans to provide care for older people, while others have not. In addition, in some practices, a practice nurse may have already been part of the practice team. Because all practices can be randomized in one of the intervention groups or in the control group, we consider these differences in elderly care at baseline as normal variations in clinical practice. In this way, both interventions are compared to the broad range of routine clinical care, enabling generalizability.

We chose a three-armed design for several reasons. First, our baseline assumption is that the U-PRIM screening followed by usual care and the combination of U-PRIM and U-CARE will both give better results than current usual care. Additionally, we hypothesize that both interventions are synergistic and that the effect of U-PRIM and U-CARE is more effective than the U-PRIM intervention alone [41].

### Outcome

The effectiveness of the interventions should be assessed on outcomes that are directly relevant for patients and their caregivers. We decided to take ADL functioning as measured with the Katz ADL index as the primary outcome. ADL functioning is generally reported as the most important parameter in the lives of older people [3]. The Katz ADL index is widely used in studies of prognosis and effects of treatments [36,42].

Additionally, a broad array of relevant secondary outcomes will be assessed to evaluate both interventions. These will be measured based on a combination of self-report, proxy report and data extraction out of routine healthcare data.

### Recruitment and compliance

Proper recruitment of older people for a clinical trial is often considered as complex [43,44]. To improve generalizability, it is important that not only healthy people are included but also less fit older people [3]. For logistical reasons, we opted for a postal approach of eligible patients by the participating GPs. In this approach, we tried to find the optimal balance between extensive information provision, which is strongly advised by the Institutional Medical Ethic Committee, and the need for short and simple information letters in this population. Although patients can contact their GP or the researchers for extra clarification, this postal approach might lead to some response bias with fewer cognitively impaired or frailer patients included than with a personal approach. To limit this problem, patients who do not give consent are approached by telephone two weeks after the information letter is sent, and home visits by a research assistant are offered.

Limiting informative censoring is a second challenge in elderly research. Informative censoring occurs when drop-outs happen for reasons directly related to the primary outcome [45]. In U-PROFIT, this can occur because frailer patients are more likely to die before we can evaluate functional status at the end of follow-up. To limit this problem and assess the extent of it, reasons for withdrawal will be collected, and an intention-to-treat analysis will be performed. Additionally, various retention strategies will be applied, e.g., home visits, interviews by phone when a postal questionnaire is difficult, small incentives, such as a U-PROFIT pen, and a newsletter to keep patients informed about the project.

### Development of the U-PRIM system

The U-PRIM system uses criteria that are known from literature to be linked to frailty, disability and morbidity and that have been selected by a local GP focus group as relevant in daily clinical practice [2,46,47]. Small pilot studies have shown that the current U-PRIM criteria identify a significant number of patients at high risk for frailty. However, the psychometric properties of U-PRIM and exact cut-off values for clinically relevant risk groups still have to be further assessed. The influence of EMR data quality on the U-PRIM output should also be examined [48].

While preparing for the U-PROFIT trial, major effort was put into building the software, implementing the U-PRIM system and testing it. However, during the trial, technical aspects of the U-PRIM system may need to be adjusted.

This might influence the current system of use and acceptance during the trial. We will assist participating centers by means of manuals, ICT assistance, and proactive contact after report generation to check for any content related questions or user feedback. With updates on the practical implications of ongoing U-PRIM research, we hope to keep all participating primary care providers on board. In this way, the U-PRIM system can be further developed into an easy-to-use frailty screening instrument that contributes to efficient and proactive panel management care. Requiring only sound EMR registration habits and periodic data upload, the U-PRIM system is an ideal candidate for efficient risk stratification of older people in primary care.

### Feasibility and adherence

The U-CARE program is a complex, multifactorial intervention with multiple components. In the trial, U-CARE will be provided by over 20 practice nurses and over 100 doctors, and optimal implementation is vital. By means of an extended training program and ongoing education during the trial, we aim for a uniform baseline level of knowledge and skills among the practice nurses. However, motivation for proactive care provision and professional experience with older patients can be different within the group of GPs and practice nurses. These differences reflect daily clinical practice, so general conclusions about the effectiveness can be drawn. However, the effectiveness may differ in relation to characteristics of health care professionals. For that reason, we will perform subgroup analyses.

Finally, this program is based on a proactive care approach. Some patients will appreciate the active interference of care providers, but other patients might not and consider it as patronizing. Possible benefits of a proactive outreach should therefore clearly outweigh the unwanted burden it may put on others.

### Strengths

Despite many challenges, we think that U-PROFIT offers many opportunities. First, the design of a three-armed, cluster randomized trial enables us to investigate the effectiveness of both interventions separately as well as in combination. Secondly, current literature recommends that trials on frailty should target persons aged 70 and older, because in younger age groups, frailty prevalence is thought to be too low [3]. However, during the development of U-PROFIT, general practitioners suggested to lower the age threshold for inclusion to 60. A substantial part of the ageing population in the practices consists of first generation immigrants of non-Dutch origin. In these elderly individuals, who often came to Holland for physical labor, frailty is reported to appear at a relatively young age [7]. With the inclusion of patients aged 60 years and older in our study, we include the group most relevant in current clinical practice.

The frailty index score is demonstrated to be a valuable indicator of the 'frailty state' of an individual. Frailty indices constructed differently, with different deficit content and considering different numbers of deficits, yield closely related results [25]. In this trial, we aim to demonstrate that the frailty index can be used for structured risk assessment in primary care practice, using routine care data.

For optimal implementation of the U-CARE intervention, we will maintain a training and supervision process of the practice nurses during the trial. In monthly meetings, special attention will be paid to collaboration between nurses and GPs to achieve optimal functioning of this important team. In addition, lectures and education about geriatric health problems will be performed. During regular project meetings, research updates will be provided to inform nurses and GPs.

While the intervention in non-pharmacological intervention studies is often poorly described, the interventions in the U-PROFIT trial consist of well-defined and thoroughly designed components. This will safeguard the reproducibility of the intervention program once the effectiveness is established.

Although various challenges have to be addressed, the U-PROFIT trial offers excellent opportunities for a valid scientific evaluation of a structured and integrated approach to improve physical functioning in frail older people in primary care. Once proven effective, it can be broadly implemented in daily clinical practice.

### Trial status

Data collection started in October 2010 and will end in March 2011. The results of this study will be expected in spring 2013.
